## Methods/design

### Recruitment and study design

This prospective, single-center pilot study is performed at the Department of Radiation Oncology at the University Hospital of Heidelberg for patients with spinal bone metastases with indication for radiotherapy. As shown in Fig. 1, participants will be randomized into two groups: one group receiving intensity-modulated radiotherapy treatment (group A) and the other conventional external beam radiotherapy (group B).

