### Data collection and follow-up period

During study observation, patient data are collected before the start of radiotherapy treatment (t0), at the end of treatment (t1), and in the follow-up period at scheduled visits in our department at time points of 3 months (t2) as well as 6 months (t3) after completion of treatment (Figs. 1 and 2).

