### Statistical analysis and randomization

This trial is being performed as a pilot study; in the calculation for statistical analysis a total of about 30 patients in each treatment group is considered an appropriate sample size. Due to the explorative character of this study, it is not possible to estimate the total number of cases. However, with a scheduled number of 30 patients per group, it will be possible to detect a standardized mean-value effect (Cohen’s *d*) of 0.8 with a power of 80% and an alpha significance level of 5%. A blocked randomization is used to allocate each participant into group A or B before start of treatment. All variables were analyzed descriptively by tabulation of the measures of the empirical distributions. According to the scale level of the variables, means, standard deviations, and medians as well as minimum and maximum or absolute and relative frequencies, respectively, will be reported. Additionally, for variables with longitudinal measurements, the time courses of individual patients will be analyzed and summarized by treatment groups. Descriptive *p* values of the corresponding statistical tests comparing the treatment groups will be given. The Wilcoxon signed rank test will be used to compare changes in group difference. The Cohen’s effect size (ES) will be assessed for clinically relevant change in questionnaire measures (<0.3 low, 0.3–0.7 moderate, >0.7 strong difference). Moreover patient data are collected in table form at the above-mentioned time points for all completed questionnaires. All statistical analyses will be performed with SAS software v 9.3 or higher (SAS Institute, Cary, NC, USA).

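### The Wilcoxon signed rank test is assigned to changes in group difference, but groups A and B are independent and the test can validly assess only change within a group

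*Protocol article*

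**What the plan says.** Under the heading on recruitment and study design, "participants will be randomized into two groups": group A receives intensity-modulated and group B conventional radiotherapy. The statistical section adds: "A blocked randomization is used to allocate each participant into group A or B before start of treatment". No crossover, matching or pairing of A patients with B patients is described.

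Each patient is measured repeatedly, before treatment (t0), at its end (t1), and 3 and 6 months later (t2, t3), so within-patient changes exist. For such variables, "the time courses of individual patients will be analyzed and summarized by treatment groups".

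Two consecutive sentences then deal with testing. The first promises descriptive "p* values of the corresponding statistical tests comparing the treatment groups will be given", without naming the tests. The second names the only test in the article: "The Wilcoxon signed rank test will be used to compare changes in group difference". The sentence after that turns to Cohen's effect size for change in questionnaire measures.

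**The concern.** The signed rank test ranks the absolute values of a single set of differences and asks whether they are centred on zero. In a parallel-group trial the only natural differences are each patient's own changes from t0. Applied to those, separately by arm or pooled, the test asks whether patients changed. It does not ask whether A changed more than B.

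To make it compare the arms, each A patient would have to be paired with an unrelated B patient. The p value would then depend on an arbitrary choice of pairs, and patients without a partner would be lost if the arms differ in evaluable number. Nothing in the article suggests this.

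The sentence therefore gives a test of change over time a purpose worded as a group comparison. An analyst who follows it could report one p value per arm and leave readers to treat significance in one arm only as a treatment effect. Both arms receive 30 Gy in 3 Gy fractions and may well change in the same direction, which is the setting in which that inference misleads.

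**Working it through.** **Inputs from the article.** Two randomised parallel groups; 30 patients per group; Cohen's d = 0.8; power 80%; alpha 5%; measurements at t0 to t3.

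**Assumptions, because the article gives no figures.** Two-sided testing; normally distributed change scores with SD 1; a range of true changes; all 30 patients per arm evaluable.

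**1. The plan's own figure.** For two independent means, n per group = 2(1.960 + 0.842)² / 0.8² = 2 × 7.85 / 0.64 = 24.5, so 25. The exact t-test calculation gives 25.5, so 26. With 30 per group, power is Φ(0.8 × √15 − 1.96) = Φ(1.14) = 87% by the normal approximation and 86.1% by the exact t. The detectable d at 80% power is 0.74. The stated 80% is met with some margin. That is conservative and not an error.

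**2. Same true change in both arms, so no group difference.** Let p be the chance that the within-arm signed rank test rejects. The arms are independent, so the chance that exactly one arm is significant is 2p(1 − p). Simulated p is about 0.05 at no change, 0.18 at 0.2 SD and 0.46 at 0.36 SD. For these, 2p(1 − p) is 2 × 0.05 × 0.95 = 0.095, 2 × 0.18 × 0.82 = 0.30 and 2 × 0.46 × 0.54 = 0.50. Direct simulation agrees within simulation error:

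| True change in both arms | Significant in one arm only | Rank-sum test rejects |
|---|---|---|
| 0 | 9% | about 4-5% |
| 0.2 SD | 29% | about 4-5% |
| 0.36 SD | 49% | about 4-5% |
| 0.5 SD | 40% | about 4-5% |
| 0.6 SD | 22% | about 4-5% |
| 0.8 SD | 3% | about 4-5% |

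The curve peaks near 50%, where p is near one half, and falls away on both sides.

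**3. Signed rank test on the pooled changes.** With an equal change of 0.4 SD in both arms, it rejects in about 84% of trials and the rank-sum test in about 4%. With changes of +0.4 and −0.4 SD, a true difference of 0.8 SD, it rejects in about 3-4% and the rank-sum test in about 84-85%. The pooled test responds to change over time and misses a group difference when the changes cancel.

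**4. Arbitrary A-B pairs.** With 30 against 30, the signed rank test on such pairs keeps a type I error of about 5% and has about 83-84% power at d = 0.8. The objection to it is therefore the dependence on an arbitrary pairing and the loss of unpaired patients. Average power at equal sizes is not the problem.

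**5. After the fix.** The rank-sum test with 30 per group and d = 0.8 has simulated power of about 84-85%, above the stated 80%.

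**The case against.** The best defence is that the sentence means change over time within each group. There are four time points, individual time courses have just been mentioned, and the next sentence concerns change in questionnaire measures. For that purpose the signed rank test is valid. The between-group tests would then be the unnamed ones promised one sentence earlier, and naming each of them is something an article may leave to the full protocol or SAP.

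Part of this stands. The article does promise between-group tests separately, so it would be wrong to conclude that the signed rank test is the only group comparison planned, and the lack of names for the others is no finding. The defence does not rescue the sentence itself. Its stated object is the group difference, and it follows directly on the sentence about comparing the groups. If within-group change was meant, the sentence describes the analysis wrongly.

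A reader might also infer that the primary analysis is invalid. The article does not support that. The primary endpoint is CTCAE toxicity at 3 months; the sentence speaks of changes and does not mention toxicity. Nor does the article propose to infer a treatment effect from significance in one arm only. The figures for that show what could happen if within-arm tests stood in for a group comparison, and they depend strongly on the assumed change: small at 0.8 SD, largest near 0.36 SD.

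**Conclusion.** The sentence is wrong as written. It names a paired or one-sample test for a purpose worded as a comparison of changes between two independent groups. This goes beyond missing detail, because a specific test is named and does not fit the design.

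The weight is moderate: should be fixed. The trial is an exploratory pilot, its p values are descriptive, no decision rule hangs on this test, and the wording is open to a within-group reading. The point affects comparisons of change scores. It would reach the primary analysis only if the same test were used for toxicity, which the article does not say.

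Under the assumptions above, discordant within-arm results with no true group difference occur in about 3% to 49% of trials across the changes examined, against about 4-5% false rejections for the rank-sum test. The conclusion that the test does not fit the design does not depend on these figures.

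**What to change.** Replace the sentence with, for example:

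> Changes from t0 are compared between groups A and B with the two-sided Wilcoxon rank-sum (Mann-Whitney) test (tie-corrected or exact for ordinal grades; Fisher's exact or chi-squared test for yes/no outcomes), with an estimated difference and 95% CI. The signed rank test is used only to describe change from t0 within a group.

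If the full protocol or SAP already names a two-sample test, align the wording of the two documents. If it repeats the published sentence, correct it there before the analysis. The article reports that recruitment was not yet complete.

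The cost is one sentence. It needs no further patients, no new data and no change to the sample size.

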## Discussion

This prospective, single-center pilot trial performed at the Department of Radiation Oncology at the University Hospital of Heidelberg assesses radiation-induced toxicity 3 months after radiotherapy in patients with spinal bone metastases by comparing intensity-modulated radiotherapy versus conventional external beam radiotherapy. Especially in this palliative treatment setting a technical approach to a limited extent of side effects and a higher relief of symptoms is needed to result in higher quality of life for palliative patients. Furthermore, this explorative study analyzes the differences seen in bone sclerosis, quality of life, spinal stability, and local control as well as clinical symptoms such as fatigue, pain relief, or neurological deficits between the two treatment groups.

### Trial status

Patient recruitment has not yet been completed.

## Abbreviations

CRF: Case report form
CT: Computed tomography
CTCAE: Common Toxicity Criteria for Adverse Events
CTV: Clinical target volume
GCP: Good Clinical Practice
Gy: Gray
IMRT: Intensity-modulated radiotherapy
OAR: Organ at risk
PTV: Planning target volume
RT: Radiotherapy
SAE: Serious adverse event
VAS: visual analog scale
VMAT: Volumetric arc therapy
